## Background

1

Adolescence and young adulthood represent developmental periods characterized by increased exploration and risk-taking behavior including alcohol misuse (Casey et al., 2008; Steinberg, 2008). In adolescents and young adults, alcohol misuse is a leading global risk factor for death and adverse effects, significantly impacting individuals and their social environments (Nutt et al., 2010). Early initiation of alcohol use has been associated with a range of adverse outcomes, including poorer cognitive functions, mental health problems, and increased vulnerability to developing substance use disorders (Danpanichkul et al., 2025; Spear, 2018).

Although evidence-based treatments for alcohol use disorder (AUD) exist, their effectiveness is limited by, amongst others, insufficient access and low motivational appeal. As a result, many patients remain untreated or without optimal care (Ritter et al., 2019). Even among those who do receive treatment, non-response and high relapse rates are common (Bottlender and Soyka, 2005; Ray et al., 2019). One way to narrow the treatment gap is to bring optimized interventions closer to patients, which can be achieved through web-based interventions delivered on patients’ mobile phones. Such low-threshold approaches increase the capacity to reach a larger proportion of patients (Smit et al., 2011) and may be highly appealing to younger, “digital native” patients.

Neuroscientific models of AUD and other addictive disorders highlight an imbalance between sensitized appetitive system and weakened inhibitory control (Volkow and Baler, 2014; Wiers et al., 2007). Patients with AUD often exhibit impaired inhibitory control, particularly when exposed to alcohol-related cues (Smith et al., 2014; Stein et al., 2018). Reduced inhibitory control is more pronounced in adolescence due to the ongoing maturation of the prefrontal cortex (Wiers et al., 2007). Conventional psychotherapeutic approaches do not directly address these automatic, cue-triggered processes. However, effective modification of the underlying neuronal circuits should include repetitive, implicit learning to counteract automatized appetitive processes (Lindenmeyer, 2010; Stacy and Wiers, 2010; Wiers et al., 2007).

Translating these findings into a therapeutic application, alcohol-specific inhibition training (Alc-IT) directly targets these crucial processes. Alc-IT refers to computerized interventions that aim to strengthen inhibitory control in response to alcohol-related cues. To date, most studies have implemented a modified Go/NoGo paradigm, in which alcohol-related stimuli are consistently paired with a stopping response. The theoretical rationale is to counteract automatic approach tendencies toward alcohol by training cue-specific inhibitory control (Batschelet et al., 2020). After a series of preclinical proof-of-concept studies (see Batschelet et al., 2020 for a review), Alc-IT has led to promising results in a first multicentric, double-blind, randomized-controlled clinical trial (RCT). In this study, it reduced drinking in a sample of inpatients with AUD (Stein et al., 2023; but see Schenkel et al., 2023). Alc-IT was originally intended to modify neurophysiological alterations that had been linked to poor inhibition in AUD. Therefore, it is of high interest to monitor whether Alc-IT modifies these crucial processes (i.e., whether Alc-IT displays the expected neurophysiological effects).

At the neurophysiological level, inhibitory control is often studied with a Go/NoGo task. Two event-related potentials (ERP), the N2 and P3 components, reliably appear during NoGo trials (Campanella et al., 2019b; Zhang et al., 2021). The NoGo N2 is a frontocentral negative peak around 200–400 ms after stimulus onset, reflecting conflict monitoring (Donkers and van Boxtel, 2004; Huster et al., 2013). The NoGo P3, a frontocentral positive peak around 300–600 ms after stimulus onset, reflects actual inhibitory control (Fallgatter and Strik, 1999; Smith et al., 2008). Studies in healthy participants show that inhibition training can alter the N2 (Benikos et al., 2013; Schapkin et al., 2007; Schroder et al., 2020). Findings comparing patients with AUD and healthy controls on NoGo N2 and P3 have been inconsistent (Colrain et al., 2011; Dubuson et al., 2023; Kamarajan et al., 2005; Pandey et al., 2012). In contrast, studies focusing on alcohol-related Go/NoGo tasks revealed clinically relevant results: Alcohol-related NoGo N2 amplitudes increase with craving and reduced NoGo P3 predicts relapse (Batschelet et al., 2021; Campanella et al., 2019a; Petit et al., 2014; Stein et al., 2018).

However, the application of Alc-IT in adolescent and young adult populations, especially in mobile formats, remains unexplored. Computerized interventions such as Alc-IT can be a cost-effective add-on to traditional relapse prevention strategies. To fully unlock the potential of these interventions, they need to be both appealing and easily accessible for patients. Furthermore, they should be integrated into comprehensive, evidence-based programs, and implemented in a way that optimally targets the underlying neuronal processes (Holmes et al., 2018; Wiers et al., 2018). Delivering Alc-IT via a mobile app is one way to expand its availability beyond the residential treatment settings. This approach has worked for similar forms of cognitive bias modification, such as approach bias modification (Laurens et al., 2020; Manning et al., 2021; Prior et al., 2021). The present project administers for the first time a newly developed, app-based version of Alc-IT in addition to outpatient treatment as usual in a sample of adolescents and young adults with AUD. The study has three objectives:

### Primary objective

1.1

#### Objective 1: assessing feasibility of Alc-IT

1.1.1

Feasibility will be assessed by recruitment and completion rates. The hypothesis regarding feasibility, albeit not requesting inferential statistics, are formulated according to the relevant guidelines (Eldridge et al., 2016). The expectations are based on (a) the mean percentages reported in earlier studies with similar interventions (Manning et al., 2021; Stein et al., 2023) and (b) the admission rates at the participating treatment centers (see footnote 1):

Hypothesis for objective 1

*H1*: We expect promising feasibility as indicated by successful recruitment of up to 210 patients, ≥ 62% completion rates of the core training phase, and ≥43% completion of the booster trainings phase.

Additionally, we will document adherence (number of completed training sessions), occurrence of adverse events, and whether participants receive Alc-IT as intended (i.e., as an add-on to standard care).

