### Study population

2.2

A total of up to 210 adolescents and young adults with AUD currently undergoing outpatient treatment or (online) counselling in one of 5 specialized treatment settings within Switzerland will be recruited.

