### Sample size determination

2.5

Note that the present feasibility RCT is not designed to statistically test hypotheses regarding effectiveness outcomes but will rather yield preliminary findings into the effect size to be expected in a future full scale RCT (Eldridge et al., 2016; Thabane et al., 2016; Thabane and Lancaster, 2019). Sample size determination followed recommendations for sample sizes in pilot and feasibility trials that allow for an acceptable estimation of future effect sizes. These recommendations suggest that for small effects, sample sizes ranging from 25 to 75 per study arm are sufficient (Whitehead et al., 2016). Given the recruitment estimation in the five treatment centers^1^, we expect to collect complete data for drinking behavior outcome from 90 patients, which aligns with these recommendations.

For the EEG sub-study, a power analysis was conducted. Using the observed neurophysiological effect size of 0.255 in our prior study (Tschuemperlin et al., 2019) as an estimate and adapting power analyses performed with R to randomization statistics (Manly, 2007), the relevant effects can be detected with a power of 0.8 and alpha-level of 0.05 starting from a sample size of 55. Therefore, complete data will be collected from 60 patients in the EEG sub-study.

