#### Objective 1 – feasibility of Alc-IT

2.12.1

Following the CONSORT guidelines’ extensions for pilot and feasibility trials (Eldridge et al., 2016), feasibility outcomes will be assessed primarily using data on recruitment and completion rates (indicating attrition), and additionally with treatment adherence, and adverse events. For these indicators, the parameters recommended in the CONSORT guidelines (such as means, data distributions, and percentages as well as narrative descriptions) will be reported. Failure to meet the above-defined indicators for promising feasibility will indicate that H1 cannot be confirmed. No inferential statistical testing will be performed for feasibility outcomes.

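### The recruitment indicator in the primary feasibility hypothesis is a ceiling of 210 with no minimum, so as written it cannot fail

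*Protocol article*

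**What the plan says.** Section 1.1.1 of the protocol article states H1 with three indicators. The first is recruitment: "We expect promising feasibility as indicated by successful recruitment of up to 210 patients". The other two are completion: "≥ 62% completion rates of the core training phase, and ≥43% completion of the booster trainings phase". The section says that the expectations rest partly on "the mean percentages reported in earlier studies with similar interventions" and partly on admission rates at the centers, for which it refers to footnote 1. Section 2.2 repeats the recruitment wording: "A total of up to 210 adolescents and young adults with AUD".

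Section 2.12.1 attaches a consequence: "Failure to meet the above-defined indicators for promising feasibility will indicate that H1 cannot be confirmed". It adds: "No inferential statistical testing will be performed for feasibility outcomes". The reporting it lists is "such as means, data distributions, and percentages as well as narrative descriptions".

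Section 2.5, again referring to footnote 1, says "we expect to collect complete data for drinking behavior outcome from 90 patients". The Discussion (section 3) names harder recruitment as a potential risk and gives early detection of problems with recruitment, usability and attrition as a reason for the feasibility design.

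**The concern.** Section 2.9.3 makes recruitment and completion the two measures of the primary outcome, and section 2.12.1 assumes that each indicator can be missed. The recruitment indicator gives an upper limit and no lower one, so the two sections do not fit together: a failure rule is attached to something that has no failing value. Poor recruitment could be described in the report, but it could not count against H1. If a minimum is chosen only once the count is known, it will not be a prespecified criterion.

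The completion indicators have a lesser weakness. They can fail, but they are cut-offs applied to an observed percentage, with no stated allowance for sampling error. If an app truly performs at the threshold level, chance largely decides the verdict.

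**Working it through.** **Recruitment.** Let N be the number recruited. Read literally, the indicator is N ≤ 210. It is met for N = 0, 30, 90, 200 and 210 alike, so the failure clause of section 2.12.1 can never apply to it.

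**The plan's own figure.** The expected number with complete drinking data is 90 (section 2.5). Multiplying 210 by the booster threshold gives 210 × 0.43 = 90.3, which rounds to 90. In reverse, 90 / 0.43 = 209.3. So about 210 recruits are needed to reach 90 at that rate, and 210 looks like a target. The link is an inference, because footnote 1 is not in the text at hand.

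**Completion: inputs.** The thresholds are 62% and 43% (section 1.1.1). The article does not state the denominator. I take n = 210 (all recruited) as the main case and n = 105 (one arm, assuming 1:1 allocation) as a check. The true rates are assumed equal to the thresholds, and booster completers are assumed to be a subset of core completers.

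**Minimum counts at n = 210.** Core: 0.62 × 210 = 130.2, so 131 are needed. Booster: 0.43 × 210 = 90.3, so 91 are needed.

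**Single criteria (exact binomial).**
- P(X ≥ 131 | n = 210, p = 0.62) = 0.485
- P(X ≥ 91 | n = 210, p = 0.43) = 0.488

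**Both criteria (nested).** The sum runs over c = 131 to 210:

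P(both) = Σ P(C = c | 210, 0.62) × P(B ≥ 91 | c, 0.43/0.62) = 0.356

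Hence 1 − 0.356 = 0.644, so H1 is unconfirmed about 64% of the time. If the two phases were independent, P(both) would be 0.485 × 0.488 = 0.237. With n = 105 the nested value is 0.341. Over the values of n tried from 60 to 210 it lies between 0.34 and 0.40, so the result does not depend on the unstated denominator.

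**Away from the thresholds.** Both true rates are shifted together, nested case:

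| Shift (points) | P(both), n = 210 | P(both), n = 105 |
|---|---|---|
| −10 | <0.001 | 0.004 |
| −5 | 0.03 | 0.06 |
| −3 | 0.10 | 0.14 |
| 0 | 0.36 | 0.34 |
| +3 | 0.72 | 0.60 |
| +5 | 0.88 | 0.76 |
| +10 | 0.997 | 0.97 |

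At n = 210 the joint probability passes 0.50 at +1.2 points and 0.80 at +3.9 points.

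**Precision at the minimum counts (Wilson 95%).** 131/210 = 62.4% (55.7 to 68.7); 91/210 = 43.3% (36.8 to 50.1).

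**The case against.** The best defense is that 210 is obviously the intended target: H1 speaks of successful recruitment, and 210 × 0.43 reproduces the 90 in section 2.5. On that view this is loose wording and not a broken design. Footnote 1 may also give a period or a target. Much of this stands, and it is why the point is moderate. It does not rescue the sentence, because H1 itself has to be assessable, and both H1 and section 2.2 state a ceiling.

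On completion, the defense is that a feasibility trial needs no test, that the reporting list in section 2.12.1 is illustrative, and that intervals may be given in the full protocol or analysis plan. That is fair: barring inferential tests does not bar intervals. What remains is that the article states a yes-or-no verdict on H1 and no allowance for precision in reaching it.

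A reader might infer more than the article supports:
- **That H1 fails to answer the primary question.** The completion indicators can fail. Rates will also be reported alongside adherence, adverse events, usability and acceptability.
- **That H1 decides whether a full trial follows.** No section says so. The stated aim is to inform later trials.
- **That the completion rule is worse than a coin flip.** Each criterion alone is about even. Only the joint rule falls below one half, and only with true rates below, at or within about 1 point above the thresholds (n = 210).
- **That 62% and 43% are the means of the earlier studies.** Section 1.1.1 says only that the expectations are based on those means and on admission rates.
- **That 90/210 = 42.9% misses the 43% threshold.** This is rounding of 90.3, and it compares complete drinking data with booster completion, which are different quantities.

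**Conclusion.** The recruitment point holds on the text alone: the indicator has no minimum, cannot fail as written, and conflicts with the failure clause in section 2.12.1. That 210 was meant as a target is likely but inferred.

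The completion point is secondary and conditional. If the true rates equal the thresholds and booster completers are nested in core completers, H1 would go unconfirmed about 64% of the time at n = 210. The rule still carries information, because five points below or above the thresholds the joint probability of passing is 0.03 or 0.88. Only a band of a few points around the thresholds is left largely to chance.

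Severity is moderate. The primary hypothesis is affected, but the design, data collection and sample size are not.

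**What to change.** 1. In sections 1.1.1 and 2.2, state whether 210 is a target or a cap. In H1, replace the ceiling with a minimum number recruited within the planned recruitment period. The plan's own figures point to about 210 as the target. The minimum itself is for the sponsor to set, since the admission estimate in footnote 1 is not in the text at hand. Set it before results are known.
2. In section 2.12.1, report a 95% interval with each completion rate. Read a near miss, where the interval still includes the threshold, as inconclusive and not as failure.
3. Do not require the whole interval to lie above the threshold. At n = 210 that would need 144/210 (68.6%) core and 105/210 (50.0%) booster completers. With true rates of 62% and 43%, both would be reached with probability of only about 0.008.

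The cost is a few sentences, with no change to design, data or sample size. The downside is a less clear-cut verdict when a rate falls close to its threshold.

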### Secondary objectives

1.2

#### Objective 2: gain preliminary findings regarding the effectiveness of Alc-IT on a drinking outcome

1.2.1

The second objective is to obtain preliminary evidence regarding the effects of Alc-IT on drinking behavior as an add-on to standard care. Unlike the original Alc-IT assessed in inpatient settings with supervised sessions (Stein et al., 2023), this app-based version allows independent use in everyday contexts. This study thus aims to gain preliminary insight into the effectiveness on drinking behavior of Alc-IT as an add-on to standard care in adolescents and young adults with AUD. As the international CONSORT guidelines state that formal hypothesis testing for effectiveness is not recommended for pilot and feasibility trials (Eldridge et al., 2016), no hypotheses (H2) for this secondary objective are formulated. However, the research aim here is to describe Alc-IT’s effects on drinking behavior, as indicated by change in percentage of days abstinent and change in heavy drinking days (both assessed with the timeline follow-back method, Sobell and Sobell, 1992) in terms of effect sizes and measures of uncertainty.

#### Objective 3: EEG sub-study – investigate the neurophysiological effects of Alc-IT within a subsample

1.2.2

The third objective is to investigate whether app-based Alc-IT can modify the neurophysiological anchorage of alcohol-specific inhibition. Such an effect would indicate that the more flexible administrable version of Alc-IT is also effective at normalizing crucial neurophysiological alterations. Building on the fact that online interventions are typically characterized by a higher variation in sessions completed (Manning et al., 2021), we will also investigate whether the neurophysiological effects vary with the number of sessions completed. This analysis will yield valuable insight regarding the optimal number of training sessions, for which evidence-based information is still lacking.

Hypothesis for objective 3:

*H3*: We expect that in patients receiving Alc-IT, the topographical difference between neutral and alcohol-related NoGo trials in the P3 component will be reduced from pre- to post-training to a larger extent than in the control group.

Furthermore, we exploratorily investigate whether baseline levels of these neurophysiological parameters, the personality trait impulsivity, or performance levels during training function as moderators of potential treatment effects.

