#### Secondary outcomes

2.9.4

*Drinking behavior* is indicated by change in percentage of days abstinent and percentage of heavy drinking days. These indicators will help describe the preliminary effects of Alc-IT on drinking behavior and will be assessed using the timeline follow-back method (TLFB) at baseline (T1), 1-month (T4) and 3-month follow-up (T5). TLFB (Sobell and Sobell, 1992, 1995) is a procedure to aid recall of past drinking. Providing a relatively accurate estimate of one’s drinking, the TLFB is considered the gold-standard in assessing past drinking behavior. The TLFB will be administered by a telephone interview.

In the EEG sub-study, outcomes include *neurophysiological measures of inhibitory activity*, specifically changes in the N2 and/or P3 components of the event-related potential derived from NoGo trials (see 2.10 for task details and 2.11/2.12 for ERP computation). Additionally, the number of completed sessions, baseline neurophysiological parameters, impulsivity, or performance levels during training will be exploratorily assessed as moderators of the neurophysiological effects of Alc-IT. The topography of the P3 component, featured in hypothesis H3, is the main parameter of interest, while amplitude of the P3 component, as well as topography and amplitude of N2 will be assessed exploratorily.

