#### Objective 3 – EEG sub-study: investigating the neurophysiological effects of iAlc-IT

2.12.3

Statistical comparisons of amplitude and topography of the N2 and P3 components (~150–850 ms) will be performed using the RAGU software package for whole-scalp randomization-based statistics, with exact time windows for N2 and P3 determined via microstate segmentation (Koenig et al., 2011, 2014). To test hypothesis H3, a three-way interaction between group (Alc-IT, Con-IT), picture type (alcohol, neutral), and time point (pre-, post-training) on the P3 topography will be examined by subjecting the difference ERPs to a topographical analysis of variance (TANOVA). Additional exploratory analyses will investigate whether neurophysiological effects are moderated by the number of completed sessions, baseline ERP characteristics, impulsivity scores, or training performance indices.

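### Sessions completed and training performance arise after randomisation, so analysing them as moderators cannot inform an optimal number of sessions

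*Protocol article*

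**What the plan says.** All references are to the protocol article.

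- **Section 1.2.2 (Objective 3)** notes that session counts vary more in online interventions and continues: "we will also investigate whether the neurophysiological effects vary with the number of sessions completed". The next sentence claims: "This analysis will yield valuable insight regarding the optimal number of training sessions, for which evidence-based information is still lacking". That sentence carries no caveat. The section also asks whether baseline neurophysiology, impulsivity or "performance levels during training function as moderators of potential treatment effects".
- **Section 2.9.4 (Secondary outcomes)** puts all four variables on one list: "the number of completed sessions, baseline neurophysiological parameters, impulsivity, or performance levels during training will be exploratorily assessed as moderators".
- **Section 2.12.3 (Objective 3 analysis)** repeats the plan: "Additional exploratory analyses will investigate whether neurophysiological effects are moderated by the number of completed sessions", followed by baseline ERP, impulsivity and training performance.
- **Section 2.4** randomises participants after T1 to one of two training versions, and nothing else is randomised.
- **Section 2.6 and Table 1** give both arms six core sessions between T2 and T3 and six more after T4. EEG is recorded at T2 and T3 only. Participants with persistent adherence problems are telephoned.
- **Section 2.7** states that the two versions share layout, stimuli and cues and differ only in how picture types are paired with Go and NoGo cues.

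**The concern.** A moderator of a randomised effect should be fixed before treatment starts. Baseline ERP (T2, before training) and impulsivity (T1) meet that condition. Sessions completed and performance during training do not.

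For sessions, whatever leads a participant to complete more of them (motivation, severity and current drinking are plausible examples) may also act on the post-training EEG. A relation between sessions and EEG change can then appear without any effect of the sessions themselves. For performance, the training version can alter the score, so the score is partly a result of the treatment whose effect it is supposed to modify.

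The article describes the study as groundwork for a full-scale trial (Sections 2.5 and 3). A session slope presented as evidence on the optimal number could be read as a dose-response relation when that trial is planned.

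**Working it through.** **1. Is session number an assigned dose?** Section 2.4 randomises the version only, and Section 2.6 assigns six core sessions to everyone. All variation in sessions before T3 is therefore departure from one common assignment. It comes from independent everyday use (Section 1.2.1) and is partly offset by telephone contact that is itself triggered by poor adherence (Section 2.6). No contrast between session numbers is protected by randomisation.

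**2. What range is observed?** The programme has 6 + 6 = 12 sessions. The last EEG is at T3, before T4 and the booster block, so the count available to the EEG analysis runs from 0 to 6. An optimum above six cannot be seen at all. One below six would be inferred only from participants who did not finish.

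**3. Is performance a pre-treatment variable?** No. In Alc-IT, alcohol pictures occur only with NoGo cues, and the Go/NoGo ratio is 75/25. In Con-IT, both picture types occur with both cues equally often. In Alc-IT the picture type can therefore help to predict the required response, so accuracy and speed may differ by arm because of the arm.

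**4. How large could a spurious slope be?** The article gives no figure for this analysis; its sample size of 55 (60 planned) belongs to the main EEG effect. The following is an illustration under assumed values.

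- 60 patients, assumed 30 per arm; 4,000 simulated trials per setting; true session effect zero.
- U is an unmeasured standard normal trait, and e1 and e2 are independent standard normal errors.
- Sessions = 4.5 + 1.5 × (gU + √(1 − g²) e1), rounded and limited to 0–6.
- Outcome = gU + √(1 − g²) e2. In the last column of the table, the term gU is present in Alc-IT only.
- Tests are two-sided at 5%.

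Before rounding and truncation, the spurious within-arm correlation is g²: 0.09, 0.25 and 0.49 for g = 0.3, 0.5 and 0.7. The simulated means are close to this.

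| Loading g | Mean r within Alc-IT | Slope within Alc-IT significant | Group × sessions significant, trait acts in both arms | Group × sessions significant, trait acts in Alc-IT only |
|---|---|---|---|---|
| 0 | 0.00 | 5–6% | 5% | 5% |
| 0.3 | 0.08–0.09 | 7–8% | 4% | 7% |
| 0.5 | 0.23 | 24% | 5% | 15% |
| 0.7 | 0.46–0.47 | 77–78% | 5% | 58% |

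The comparison with Con-IT removes the bias when selection works identically in both arms. Randomisation balances the trait between arms, but it does not guarantee that the trait relates to sessions and outcome in the same way under both versions.

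**5. Would a null slope be informative?** With 30 in an arm, the correlation detectable with 80% power is tanh((1.960 + 0.842)/√(30 − 3)) = tanh(0.539) = 0.49. A flat slope would not exclude a moderate relation.

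**The case against.** The strongest defence is that Sections 2.9.4 and 2.12.3 call these analyses exploratory, that Section 1.2.2 speaks of insight and not of identification, and that moderation of an Alc-IT effect most naturally means group by sessions, where the control arm absorbs selection common to both arms. Motivation and craving are also collected at T1, T2 and T3, so some adjustment is possible, and its details may properly be left to an analysis plan that is not shown.

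Much of this stands. On the natural reading, the false-positive rate stays near 5% if selection is equal in both arms, and no single inflation figure can be given for the plan. But an exploratory label concerns strength of evidence and does not remove confounding. The sentence on the optimal number carries no such label, and adjustment would cover measured causes only.

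A reader might also infer stronger points that the article does not support:

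- **The arms train on different tasks, so performance has no common meaning.** Section 2.7 gives the same layout, stimuli and cues, with only the pairings differing. That is enough for the arm to affect scores, and no more.
- **Performance is self-selected.** That description fits sessions completed. The problem with performance is that it is measured after randomisation and may be affected by the arm.
- **The range of sessions is narrowed because "complete data will be collected from 60 patients in the EEG sub-study".** Section 2.5 states a recruitment target. It does not define complete data as six finished sessions or exclude partial completers.
- **The result will fix the next trial's session number.** No section says so.

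**Conclusion.** The claim about the optimal number should not stand as written. Session number is not randomised, the same six sessions are assigned to everyone before the last EEG, and nothing beyond six is observed. This follows from Sections 2.4 and 2.6 alone and needs no numerical assumption. Listing sessions completed and training performance as moderators beside baseline ERP and impulsivity is also wrong, because both arise after randomisation.

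The size of any bias is not known. It rests on the assumed loading, equal arms of 30, and whether selection acts alike in both arms. Over loadings of 0.3 to 0.7, a within-arm slope is falsely significant in 7% to 78% of trials. The interaction is so in about 5% under equal selection, and in 7% to 58% if selection acts only under Alc-IT. These figures show what could happen and do not estimate this trial's error rate.

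The point is confined to the interpretation of exploratory analyses. The feasibility outcome, the H3 test and the sample size are not affected.

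**What to change.** 1. **Section 1.2.2:** delete the sentence on the optimal number. Alternatively, restate it along these lines: *the association between sessions completed (at most six before T3) and EEG change will be described; it is not causal and cannot set a session number, which would require randomising the number of sessions.*
2. **Sections 1.2.2, 2.9.4 and 2.12.3:** reserve the term moderator for baseline ERP and impulsivity. Name sessions completed and training performance as post-randomisation variables.
3. **Sessions:** report a group-by-sessions association with both arm-specific slopes and their intervals. A slope found in both arms is compatible with selection. Label the result non-causal even when the slopes differ.
4. **Training performance:** report its association with EEG change within each arm only.

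The cost is wording, and the loss of one claim that the design cannot support. No data collection or sample size changes.
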